#### Mediational analysis

Exploratory mediational analysis will examine the extent to which changes in ADHD symptoms are determined by the effects of the treatment package on parents (more positive and constructive parenting or improved maternal mental health) and on children (improved inhibition and greater delay tolerance). Analysis will be conducted using regression approaches, as recommended by Valeri and Vanderweele in their 2013 paper [79] using SAS and SPSS; and path analysis using AMOS (for Windows) and Mplus (Muthen & Muthen, Los Angeles, CA.).

#### Moderator analysis

The presence of parental ADHD will be assessed using the CSS [65]. This score will be collected at baseline and an interaction term (CSS * treatment group) will be included in the mixed-effect regression models to determine whether parent training might be less beneficial for children whose parents demonstrate symptoms of ADHD. The interaction term will be considered significant for *P* < 0.05.

Risk of long-term burden as assessed by the PARI will be included in the mixed-effect regression models to determine whether this measure moderates the effect of treatment on primary and secondary outcomes.

#### Genetic moderation of parent-training effects

DNA will be collected from parents and children, to test whether parental responses to parent training in terms of changes in parenting behaviour and the parent’s responses to the child during interaction are moderated by functional polymorphisms in selected genes shown to affect parenting and ‘openness’. These will include polymorphisms that have been associated with the ADHD phenotype in genes that control serotonin, dopamine and oxytocin function (*DRD4*; *DRD2*; *5HTT-* group) will be included in the mixed-effect regression models to determine whether this measure moderates the effect of treatment on primary and secondary outcomes.

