#### Primary and secondary measures

The primary outcome measure is the SNAP-IV-P ADHD Scale (parent-completed), which will be collected at the three time points and records the frequency of occurrence of ADHD symptoms [56]. Secondary outcome measures include a child observation measure carried out by the research fellow using the Child’s Solo Play Index [27]; the teacher-completed SNAP-IV-T ADHD Scale; the teacher and parent-completed SNAP-IV ODD scale [56] and the Eyberg Child Behaviour Inventory [57], both of which are measures of noncompliant and oppositional behaviour

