#### Mediators

Factors that might play a mediating role in the effectiveness of the parenting programmes will be investigated and will be collected at all time points. Measures employed will include the expressed emotion five-minute speech sample (FMSS) [60]; the Global Impressions of Parent–child Interactions (GIPCI) observation measures, which include ‘Jigsaw’, ‘Tidy-up’ and ‘Free play’ [61,62]; the ‘Cookie delay’ task, which is a measure of inhibition [63], and the parent-completed General Health Questionnaire [64].

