### Statistical analysis

The main analyses will be performed using the intention-to-treat population. All results will be reported according to the CONSORT statement for nonpharmacological interventions [66]. The primary endpoint for the comparison between adapted-NFPP and IY will be the average ADHD score on items 1 to 18 of the SNAP-IV-P at post-treatment. The primary analysis of this endpoint will adjust for baseline SNAP-IV-P scores using a mixed-effect regression model [77] with treatment arm and time (pre- and post-treatment) as the fixed effects and therapist as a random effect. Subject to approval, this analysis will also include trial centre and recruitment tranche as randomization stratification factors. These models are especially valuable when used with longitudinal and trial data derived from parallel arms. A similar secondary analysis comparing adapted-NFPP and IY will be carried out 6 months after treatment. Secondary outcome measures, including the Child’s Solo Play Index, ECBI (Parent), ADHD SNAP-IV-T and SNAP-IV-T, together with SNAP-IV-P ODD scores, will be analyzed in the same way as SNAP-IV-P ADHD.

Subject to approval, a per-protocol analysis will also be performed. The parent will be considered to have completed the parenting programme if he or she had completed at least 8 of the 12 programme sessions. In the case of the IY programme, this will be either by attending the group or by receiving individual home-based sessions for any missed sessions.

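### The genetic section frames its hypothesis around change in parenting, but the outcomes it names for the test include no measure of parenting

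*Protocol article*

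**What the plan says.** The section headed Genetic moderation of parent-training effects gives two aims for collecting DNA. The first is "to test whether parental responses to parent training in terms of changes in parenting behaviour" is subject to moderation. The second asks whether "the parent’s responses to the child during interaction are moderated by functional polymorphisms in selected genes". In both, what is being explained is the parent's behaviour, and the genes are chosen because they are thought to affect parenting.

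The paragraph ends with the analysis. A term whose beginning is lost in the extracted text "will be included in the mixed-effect regression models to determine whether this measure moderates the effect of treatment on primary and secondary outcomes".

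Outcomes are defined under Primary and secondary measures. The primary outcome is the parent-completed SNAP-IV ADHD scale. On the rest: "Secondary outcome measures include a child observation measure carried out by the research fellow using the Child’s Solo Play Index", followed by the teacher SNAP-IV ADHD scale, the parent and teacher SNAP-IV ODD scales and the ECBI. The Statistical analysis section repeats this clinical list, including "ECBI (Parent), ADHD SNAP-IV-T and SNAP-IV-T, together with SNAP-IV-P ODD scores". Table 1 adds the service receipt inventory and the EQ-5D under the secondary outcomes.

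The Mediators paragraph of Study measures lists the expressed emotion speech sample (FMSS) and "the Global Impressions of Parent–child Interactions (GIPCI) observation measures". Both are collected at all time points.

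**The concern.** A moderation hypothesis is tested by an interaction in a model whose dependent variable is the quantity said to be moderated. Here that quantity is the parent's behaviour after training, while the models named in the same paragraph have child symptoms and other non-parenting outcomes on the left-hand side.

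Genetic moderation of child symptom change is a legitimate question, but it is a different one. Genotype could alter how far a parent's behaviour shifts without a visible interaction on symptoms. Equally, it could alter symptom response by a route that does not pass through parenting, since child DNA is collected as well. If only the named models are run, neither a positive nor a null interaction on the SNAP-IV would settle what the genetic section sets out to learn.

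**Working it through.** The article gives no figure to reproduce on this point. The check is a comparison of passages, followed by a count of tests for the remedy.

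**Step 1: does any primary or secondary outcome measure parenting?** The sources are the Abstract, Aims and objectives, Primary and secondary measures, Table 1 and Statistical analysis.

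| Outcome | What it measures |
|---|---|
| SNAP-IV-P ADHD (primary) | child ADHD symptoms, parent-rated |
| SNAP-IV-T ADHD | child ADHD symptoms, teacher-rated |
| SNAP-IV-P and -T ODD | child oppositional behaviour |
| ECBI | child problem behaviour |
| Child's Solo Play Index | child attention, observed |
| CSRI-R | service use and costs |
| EQ-5D, parent and proxy | health-related quality of life |
| Parental mental health (called a secondary outcome only in the aims) | parent's own health |

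No row is parenting behaviour or the parent's response to the child.

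**Step 2: is parenting measured at all?** Yes. The GIPCI section describes coded video of parent and child in three tasks, with parent items such as responsiveness, warmth, praise, scaffolding and criticism. This is close to the second half of the genetic hypothesis. The FMSS section rates the parent's expressed emotion. Table 1 shows both at T1, T2 and T3 (T1 and T2 only for the TAU arm).

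**Step 3: does another analysis link genotype to these measures?**
- Mediational analysis uses parenting change to explain ADHD change and describes no genotype term.
- Moderator analysis covers the CSS and the PARI.
- The treatment fidelity section covers the fidelity composite and the FSI.

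None brings genotype together with the GIPCI or FMSS.

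**Step 4: which genetic question do the named models answer?** Research question 4 asks whether the effects in the preceding questions (ADHD symptoms, other child problems, generalization to educational settings) are moderated by genetic factors. The Moderators paragraph speaks of programme effectiveness, the Abstract of increased benefit, and the Discussion of clinical response. Models on primary and secondary outcomes fit all four. They do not fit the hypothesis in the genetic section.

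**Step 5: how many tests would the remedy add?** The Moderators paragraph names six genes (DRD4, DRD2, 5HTT-LPR, COMT, MAO-A, OR-A), with DNA from parent and child. With two parenting measures:

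6 genes × 2 genotyped persons × 2 measures = 24 interaction tests per arm contrast, counting one polymorphism per gene.

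If the 5% threshold given for the CSS interaction were carried over, 24 × 0.05 = 1.2 nominally significant results would be expected per contrast with no true interaction.

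For scale, the six clinical outcomes (SNAP-IV ADHD from parent and teacher, SNAP-IV ODD from parent and teacher, ECBI taken as one, solo play) already imply 6 × 6 × 2 = 72 such tests per contrast.

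**The case against.** **The analysis sentence is damaged.** Text is missing after the start of the serotonin transporter gene name, and the model is specified just there. Text lost in reading the PDF does not count as missing from the plan. This stands as a limit: the absence of a parenting outcome is probable, not certain. The surviving outcome clause is intact and matches the wording of the two neighbouring moderator sections, so the gap most likely held the remaining genes and an interaction term.

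**Most of the article asks the broader question.** This stands too. A reader might infer that the genetic analysis answers the wrong question altogether, or that the trial's genetic aim goes untested. The documents do not support that, because the named models address genetic moderation of treatment benefit as worded in four other places. What is left without a matching test is the narrower hypothesis in the genetic section.

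**Dependent variables for a genetic substudy belong in the full plan.** This would answer an omission. Here the article does name the outcomes, and they do not match the hypothesis in the same paragraph.

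**A large power penalty.** A reader might also infer that testing on child symptoms multiplies the sample needed to detect genetic moderation of parenting. The documents give neither a genotype effect nor the strength of the path from parenting to symptoms. Such a figure would also assume that genotype acts on symptoms only through parenting. It would have to allow for the parent GIPCI test-retest reliability of 0.50 as well, which shrinks an observed standardized effect by √0.50 ≈ 0.71. No multiple can be defended from this text.

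**Conclusion.** The mismatch is real and sits within one paragraph: the hypothesis is about parenting, and none of the outcomes named for its test measures parenting. It rests on the visible text and on the listed outcomes being complete.

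The severity is low. The analysis serves a secondary objective, and the primary endpoint, sample size and main comparison are unaffected. Nothing is irretrievable, since the parenting measures are collected in all three arms at T1 and T2. What is at stake is interpretation: an interaction result on symptoms, null or not, should not be reported as evidence on genetic moderation of parental response.

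**What to change.** In the genetic section, add two dependent variables for the genotype-by-arm interaction: the GIPCI parent score and FMSS expressed emotion, each at T2 and adjusted for T1. Keep the models on SNAP-IV-P and the secondary outcomes, and state that they answer research question 4.

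Label the added models exploratory. State the number of tests, up to about 24 per arm contrast, and how multiplicity will be handled or reported.

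The cost is a few sentences and extra models on data already being collected. The price is more exploratory tests on top of an already long list, on an interaction measure of modest reliability. If the trial team does not want that, rewording the genetic hypothesis to match research question 4 would remove the contradiction, but the parenting hypothesis would then be given up.

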#### Effects as a function of treatment fidelity

Scores from the LOT and the Working Alliance Inventory will be used to calculate a fidelity composite measure (scored 1 to 3, indicating low to high fidelity). An interaction term ‘fidelity composite score * treatment group’ and, similarly, an interaction term ‘FSI * treatment group’ will be included in the mixed-effect regression models to determine whether these measures moderate the effect of treatment on primary and secondary outcomes.

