### Programme fidelity

Strategies for ensuring fidelity are incorporated as integral parts of the two parenting programmes, including training and monitoring procedures. In addition, a common approach will also be adopted to assess fidelity and integrity as required by each programme, so that these factors can be compared across treatments and their effects on outcome assessed. Procedures for optimizing fidelity relate to the selection, training and supervision of therapists and the skills to be acquired by therapists. The therapists for both programmes come mostly from a health background and are nurses with a background in child and adult mental health services (CAMHS), paediatrics or health visiting; psychologists with a background in CAMHS or behavioural management; family support workers with a background in CAMHS; or senior social workers with experience in children services. As initial training, therapists delivering both programmes will attend a residential training course focused on the techniques necessary to deliver the programme. The basic 3-day IY parent group leader workshop teaches leaders how to use the programme as preventive early intervention in a range of settings. Attending this workshop is the first step in becoming a certified group leader. Training covers three parent programmes, for parents of toddlers aged 1 to 3 years, parents of preschool children aged 3 to 6 years and parents of school-aged children 6 to 8 years old. Both sets of therapists will have ongoing supervision both locally and centrally throughout the time of the trial using face-to-face supervision, by telephone and monitoring of videotaped sessions recording their work with families. Training and supervision of IY therapists and leaders is overseen by practitioners with extensive experience of delivering IY and a clinician (JH) with extensive experience in working with the IY set of programmes and their development. Training and supervision of adapted-NFPP therapists is overseen by a clinician (MT) and a consultant nurse specializing in ADHD (CLB), both with extensive experience in conducting the NFPP and its development.

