### Fidelity measures

Session checklists and evaluation forms will be completed by therapists. Three instruments will also be used to monitor process and treatment fidelity across both programmes and their moderating effects on outcomes. Process fidelity will be measured using a modified version of the Leader Observation Tool (LOT) after treatment is finished [53]. The Working Alliance Inventory [54] will be used to look at aspects of the parent-therapist relationship during therapy. The impact of treatment on the family will be measured using the Family Strain Index [55].

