##### Leader Observation Tool (LOT: [53])

Process fidelity will be measured using a modified version of the LOT after treatment is finished. This revised version is adapted from the LOT tool used to successfully monitor the fidelity of the IY, which is delivered to parents in a group format. Random sessions from the videotaped IY and adapted-NFPP therapy sessions will be observed and coded by an independent observer, who will score adherence to content week by week as well as the process by which the programme is delivered. The LOT has high internal reliability and good code-recode and interrater reliability. Evidence of concurrent validity has also been obtained.

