##### Working alliance inventory, short form: parent and therapist versions (WAI-S: [54])

The WAI-S is a 12-item self-report measure of working alliance. The working alliance is an important part of the process of therapy, and looks at the alliance of task, goals and relationship of therapist with parent and vice versa. Most studies suggest that this alliance is usually forged within 2 to 4 weeks of the beginning of therapy. Two versions of the WAI-S are available: a client version and a therapist version. In this trial, both versions will be completed by the parent and therapist in weeks 6 and 12 of the parenting programme with each form being treated as confidential and delivered to the research office in a sealed envelope by the therapist. The authors of this measure found a correlation with outcome. The WAI-S has three subscales: goals, tasks and bond. Each subscale is scored on a 7-point Likert-type scale ranging from 1 (never) to 7 (always) and has four nonoverlapping items. Subscale scores can range from 4 to 28, to produce a total score of 12 to 84 with higher scores reflecting more positive ratings of working alliance. Internal consistency estimates of the three subscale scores, based on an initial validation sample of 124 pairs of parents and their therapists, ranged from 0.90 to 0.92 (client version) and 0.83 to 0.91. Internal consistency estimates of the total scores were 0.98 (parent version) and 0.95 (therapist version [54].

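### One 1-to-3 fidelity composite merges observed delivery (LOT) with working alliance (WAI-S), so its single interaction term cannot show which relates to outcome, and it loses information if the score has three levels

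*Protocol article*

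**What the plan says.** All references are to the protocol article.

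- **Effects as a function of treatment fidelity.** "Scores from the LOT and the Working Alliance Inventory" are combined into one measure: the scores "will be used to calculate a fidelity composite measure (scored 1 to 3, indicating low to high fidelity"). The term entered in the mixed-effect models is "fidelity composite score * treatment group". The Family Strain Index has its own interaction term; neither the LOT nor the WAI-S does.
- **Leader Observation Tool.** An independent observer codes randomly chosen videotaped sessions, "who will score adherence to content week by week as well as the process by which the programme is delivered".
- **Working alliance inventory.** This is a self-report measure that "looks at the alliance of task, goals and relationship of therapist with parent and vice versa". Its subscales combine "to produce a total score of 12 to 84 with higher scores reflecting more positive ratings of working alliance". Parent and therapist each complete it in weeks 6 and 12.
- **Fidelity measures.** The LOT is assigned to process fidelity, while the Working Alliance Inventory "will be used to look at aspects of the parent-therapist relationship during therapy".
- **Programme fidelity.** A common approach to assessing fidelity and integrity is adopted "so that these factors can be compared across treatments and their effects on outcome assessed".

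**The concern.** The article describes two instruments with different raters and different targets, says it wants the effects of such factors on outcome assessed, and then names one blended score as the only fidelity term.

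Two things follow:

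- **Attribution.** A positive interaction could come from delivery, from alliance or from both. A null one could hide an effect of either. The named term does not separate these cases.
- **Precision.** If the blend is reduced to three levels, part of the variation in the underlying scores is discarded before the model is fitted, which weakens any real association.

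What is at stake is the usefulness of a secondary moderator analysis. The primary comparison of adapted-NFPP with IY does not depend on it.

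**Working it through.** The article gives no power, information or sample-size figure for the fidelity analysis, so there is no figure to reproduce.

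**Step 1: what the single term can identify.** Let L and W be standardised LOT and WAI-S scores, and let the composite C be any fixed blend of them. The model estimates one interaction slope, on C. An effect carried by L alone, by W alone or by both produces a non-zero slope on C in each case. No distributional assumption is needed, and the point stands whether 1 to 3 means three categories or a continuous range.

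**Step 2: information kept when a score X is coded S = 1, 2, 3.** With a linear relation to outcome, the fraction kept is

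f = cov(X, S)² / (var X · var S).

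The article gives neither the distribution of the composite nor its cut-points, so both are assumptions here. Two cases by hand:

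- Normal, equal thirds: cov = 2 × φ(0.431) = 2 × 0.3636 = 0.727 and var S = 2/3, so f = 0.529 / 0.667 = 0.793.
- Uniform on 0 to 1, equal thirds: cov = 2 × 0.1111 = 0.2222, var X = 1/12 and var S = 2/3, so f = 0.0494 / 0.0556 = 0.889.

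The rest come from numerical integration:

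| Assumed shape and cuts | Information lost |
|---|---|
| Normal, best cuts (27/46/27) | 19.0% |
| Normal, 25/50/25 | 19.2% |
| Normal, equal thirds | 20.7% |
| Normal, 20/60/20 | 21.6% |
| Normal, 10/80/10 | 38.4% |
| Uniform, equal thirds | 11.1% |
| Skewed, beta(5,2): best cuts / thirds | 16.0% / 19.6% |
| Heavy-tailed, t with 5 df: best cuts / thirds | 27.4% / 31.2% |
| U-shaped, beta(0.5,0.5): best cuts / thirds | 7.7% / 8.8% |

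The article expects 127 analysed per active arm (Sample size), or 254 in total. The effective number is then about 254 × 0.793 = 201 at normal thirds, 254 × 0.889 = 226 for the uniform case and 254 × 0.616 = 156 at normal 10/80/10.

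**Step 3: the same loss as power.** Take a test with an assumed 80% power on the uncut score at two-sided 5%. Then power = Φ(2.80 · √f − 1.96).

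- f = 0.793: Φ(2.493 − 1.96) = Φ(0.53), about 70%.
- f = 0.889: Φ(2.640 − 1.96) = Φ(0.68), about 75%.
- f = 0.616: Φ(2.198 − 1.96) = Φ(0.24), about 59%.

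**Step 4: merging, before any cutting.** If only one component relates to outcome and the composite is an equal-weight mean of two standardised scores with correlation r, it keeps (1 + r)/2 of that component's information: 50% at r = 0, 75% at r = 0.5 and 87.5% at r = 0.75. If both matter equally, the linear predictor is b(L + W), which is proportional to the composite, and pooling loses nothing. The article does not say which case applies, so Step 4 supports reporting the components but gives no general size for the loss.

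**The case against.** The strongest reply is that one prespecified composite is a legitimate choice. It spares extra tests in a plan that already has parental ADHD, PARI, genetic and Family Strain Index moderators across several outcomes. It can gain power when both components matter. The constructs may also overlap, since the LOT covers process as well as content and the WAI-S covers tasks and goals as well as bond. The raw scores are collected, so separate models could be run anyway. All of this stands, and it is why the fix keeps a composite instead of replacing it.

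Three further objections limit the size of the point:

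- **Three levels is an inference.** The article gives a range and a direction, not categories or cut-points. If 1 to 3 is continuous, Steps 2 and 3 fall away and only the attribution problem remains.
- **The combining rule is not given.** A reader might infer that a family with high alliance and poor adherence must score the same as one with the reverse. That holds only under roughly equal weights; such families can score the same. The missing rule is not itself a fault, as an article may leave it to the full protocol or analysis plan.
- **The components may sit at different levels.** IY is delivered to groups of eight, so a LOT score from an IY session describes a group session, while the WAI-S is completed per parent. The calculations treat scores as one per family and are illustrative.

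A reader might also infer that at least a fifth of the information is lost. That is not a lower bound: a normal score cut at 25/50/25 loses 19.2%, and a uniform score cut at thirds loses 11.1%. Nor do the documents support a headline fall in power from 80% to 42% (0.5 × 0.793 = 0.397 kept, r = 0) or 52% (0.65 × 0.793 = 0.515 kept, r = 0.3). Those figures need equal weights, cutting at thirds, an assumed 80% start and only one component mattering.

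**Conclusion.** The point holds as a minor improvement. The one fidelity-by-treatment term that the article names cannot separate delivery from alliance, although Programme fidelity and Fidelity measures present these as factors whose effects on outcome are to be assessed. This needs no assumption about distributions or cut-points.

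The loss of information is conditional on a three-level score and a linear relation to outcome. It is about 19% to 21% for a roughly normal score cut near thirds or at the best points. It is about 11% to 38% across the uniform, skewed, heavy-tailed and unevenly cut cases, and somewhat less (8% to 9%) for a U-shaped score. At normal thirds, an assumed 80% power becomes about 70%.

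It would go too far to say that attribution is impossible in this trial. The named term does not provide it, but the data to be collected can.

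**What to change.** In Effects as a function of treatment fidelity:

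1. Keep the composite uncut, for example as the mean of the standardised LOT and WAI-S scores, and drop the 1-to-3 scoring.
2. Report beside it the separate continuous LOT-by-treatment and WAI-S-by-treatment terms, labelled exploratory.
3. State which WAI-S total is used. Two raters at two weeks give four totals per family, so the rater and the week, or a rule for averaging, need naming.

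The cost is analysis wording only, on data already being collected. The downside is a few more exploratory coefficients per outcome, to be read with multiplicity in mind and with the possible group-level nature of IY LOT scores noted. The primary analysis does not change.
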